### Quality control and data collection

All staff involved in the trial will receive training before the trial commences. The training program will include case screening, intervention method, evaluation of outcome measures, completion of case report forms (CRFs), and data management.

Two data managers with medical backgrounds will check the data recorded in the CRFs. After a data review, two research assistants will independently input the data using EpiData software (EpiData Association, Odense, Denmark). The data will then be submitted to a statistician independent from the research team for final analysis.

### Sample size and statistical analysis

The reduction in YGTSS score in the pilot trial after 12 weeks of treatment in the plum-blossom needle therapy group and HRT group was 13.12 ± 5.40 (mean ± standard deviation) and 9.50 ± 3.20 (mean ± standard deviation), respectively. Using a one-sided superiority test (α = 0.025), 30 patients will be required in each group to give a power of 80 %, allowing for a 20 % dropout (1:1 ratio).

The outcome parameters of randomized patients will be analyzed on an intention-to-treat basis. Missing data will be replaced by the last entry. All outcome measures will be analyzed by two-sided tests. All significance levels will be established at 0.05. Continuous data will be represented by the mean, standard deviation, median, minimum value, and maximum value; categorical data will be represented by percentages. A *t*-test or nonparametric test will be used for continuous data. A chi-square test or Fisher’s exact test will be used for categorical data. For analysis of safety, the chi-square test or Fisher’s exact test will be done to compare the incidence of side effects between the two groups. Analyses will be performed using SPSS version 13.0 software (SPSS Inc., Chicago, IL, USA).

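### The 80% power belongs to 24 fully observed patients per arm, not to the planned analysis of all randomised patients with last values carried forward

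*Protocol article*

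**What the plan says.** Everything needed is in the protocol article, mainly under 'Sample size and statistical analysis'.

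- **Pilot inputs.** The 12-week reduction in the needle and habit reversal training (HRT) arms "was 13.12 ± 5.40 (mean ± standard deviation) and 9.50 ± 3.20 (mean ± standard deviation), respectively".
- **Sizing.** "Using a one-sided superiority test (α = 0.025"), the text concludes that "30 patients will be required in each group to give a power of" 80%, with a 20% dropout allowance and equal allocation.
- **Analysis set.** "The outcome parameters of randomized patients will be analyzed on an intention-to-treat basis".
- **Missing values.** "Missing data will be replaced by the last entry".
- **Test.** "All outcome measures will be analyzed by two-sided tests. All significance levels will be established at 0.05". A t-test or a nonparametric test is foreseen for continuous outcomes.

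Under 'Outcome measures', the primary endpoint is the change in total tic score at week 12, and the tic scale is also scored at weeks 4 and 8. A patient lost before week 12 can therefore carry forward a baseline, week 4 or week 8 value.

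**The concern.** The dropout allowance and the missing-data rule treat the same patients in two ways. In the sizing, dropouts supply nothing, and 24 patients per arm show the full pilot effect. In the analysis, dropouts stay in with an earlier score. Dividing by 0.8 makes up for lost numbers. It does not make up for a diluted effect: if improvement is still building when a patient leaves, the carried-forward reduction is too small in both arms, the gap between the arms narrows, and the mixture of early and complete values can be more variable.

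What is at stake is how a null result is read. It would be taken as coming from a trial with 80% power, when the power of the specified analysis is not stated and may be materially lower.

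**Working it through.** **1. Reproduce the plan's figure.** Difference = 13.12 − 9.50 = 3.62. Pooled SD = √((5.40² + 3.20²)/2) = √((29.16 + 10.24)/2) = 4.438. One-sided 0.025 and two-sided 0.05 share the critical value 1.960 in the direction of interest, so sidedness does not affect the result.

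n = (1.960 + 0.842)² × (29.16 + 10.24)/3.62² = 23.6, so 24 per arm; 24/0.8 = 30 per arm. The stated figure is reproduced exactly.

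Power with 24 per arm: 80.7% (normal) or 79.0% (noncentral t). Power with 30 full-effect patients per arm: 88.5% (normal) or 87.4% (noncentral t).

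**2. Model the planned analysis.** Assumptions, none of them given in the article: 20% random dropout in each arm, unrelated to outcome; the pilot means and SDs describe fully observed patients; a dropout carries a fraction f of his or her own week-12 reduction. For an arm with mean m and SD s:

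- mean = m × (0.8 + 0.2·E[f])
- variance = (0.8 + 0.2·E[f²]) × (s² + m²) − mean²

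The two arms then enter a t-test with 30 per arm (58 degrees of freedom).

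*All dropouts carry baseline (f = 0).* Means 0.8 × 13.12 = 10.496 and 0.8 × 9.50 = 7.600; difference 2.90. Variances 0.8 × 201.29 − 10.496² = 50.87 and 0.8 × 100.49 − 7.600² = 22.63; SDs 7.13 and 4.76, pooled 6.06. Noncentrality 2.896/(6.062 × √(2/30)) = 1.85; power 44%.

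*Last entries spread evenly over baseline, week 4 and week 8, linear improvement (f = 0, 1/3, 2/3).* E[f] = 1/3 and E[f²] = 5/27. Means 11.37 and 8.23; difference 3.14; SDs 6.26 and 4.04, pooled 5.27. Noncentrality 2.31; power 62%.

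**3. The range.**

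| Last entry of dropouts | Difference | Pooled SD | Power, 30 per arm |
|---|---|---|---|
| All baseline | 2.90 | 6.06 | 44% |
| Even over baseline, weeks 4 and 8 | 3.14 | 5.27 | 62% |
| All week 4 | 3.14 | 5.05 | 66% |
| Even over weeks 4 and 8 | 3.26 | 4.78 | 74% |
| All week 8 | 3.38 | 4.45 | 82% |
| No loss of effect | 3.62 | 4.44 | 87% |

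The rows for weeks 4 and 8 assume linear improvement. If every dropout keeps the same fraction, break-even with the stated 80% lies at f ≈ 0.60.

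**4. Simulation check.** Simulated t-tests with random dropout agree: 44%, 62%, 66%, 74%, 83% and 88% in the order of the table. With exactly six dropouts per arm, the all-baseline case falls to 39%.

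**5. Sensitivity to the assumptions.**

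- *Response course.* With an assumed front-loaded response (60% of the effect by week 4, 85% by week 8), last entries split between weeks 4 and 8 give 83%; if a third of dropouts carry baseline instead, 68%.
- *Unequal dropout.* In the evenly spread case, 30% dropout in the needle arm and 10% in the HRT arm gives about 21%; the reverse gives about 93%. The reverse figure is not a real gain, because carried-forward values then create part of the difference.

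**The case against.** The strongest reply is that the arithmetic is right, that dividing by one minus the dropout rate is a customary and approximate allowance, and that the article does not claim 80% for a carried-forward analysis. That stands: this is a mismatch between two stated items, not a calculation error.

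The second reply concerns size. A reader might infer that the trial really has 62% power, or that power may fall to 44% and no lower. The article supports neither. The 62% needs linear improvement, equal random dropout and an even split of last entries. The 44% needs every dropout to leave before week 4, and it is not a floor, since six dropouts per arm gives 39% and unequal dropout can give much less.

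A reader might also infer that 80% is reached only if nearly all dropouts leave late. That does not follow either: about 60% of the effect retained is enough, and under a front-loaded response half of the dropouts can leave before week 8 with power still at 83%.

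Finally, smaller reductions among dropouts are a reasonable assumption but not a documented fact. If the pilot means already contain carried-forward values, the dilution is already in 13.12 and 9.50 and the shortfall largely disappears. The article does not say.

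None of this removes the mismatch. It limits what can be said about its size.

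**Conclusion.** The point holds as a mismatch between the basis of the sample size and the planned analysis. The 80% (79% by the t distribution) is the power with 24 patients per arm fully observed at week 12; the plan analyses all 30 per arm with last values carried forward and gives no power for that.

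Under equal 20% random dropout, power of the planned analysis is roughly 40% to 88%, on either side of the stated figure. Where it falls depends mainly on how many dropouts leave before the week 4 visit and how fast patients improve, and the article gives neither. The 62% case is an illustration, not an estimate. The matter is worth correcting but moderate: it affects the stated power and the reading of a null result, not the number of patients.

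**What to change.** Keep 30 per arm and take one of two routes.

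1. **Restate the power.** Give the power of the intention-to-treat analysis with last values carried forward, together with the assumed dropout timing and response course, and say whether the pilot means are from completers. This is wording only. The stated figure may become less favourable.
2. **Change the missing-data method.** Replace the carry-forward rule for the primary endpoint with a likelihood-based repeated-measures analysis of the observed week 4, 8 and 12 scores, and state that the 80% (79% by the t distribution) refers to about 24 patients per arm observed at week 12. This is a small change to the analysis, not wording only. It needs no new data, since those visits are already planned, but it should be documented as an amendment because recruitment has begun ('Trial status' reports two participants). It rests on dropout being explained by the observed scores.

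Neither route needs extra patients.

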### Plum-blossom needle therapy group

The acupoints were selected based on our pilot study and consensus with experienced acupuncture experts. The points will be DU20 (Baihui), DU16 (Fengfu), GB20 (Fengchi), EX-HN5 (Taiyang), BL15 (Xinshu), BL18 (Ganshu), and BL23 (Shenshu). Self-made head-detachable sterile plum-blossom needles will be used in this trial (see Fig. 3). After the skin has been wiped with 75 % alcohol, plum-blossom needles will be tapped perpendicularly on the skin at the selected acupoints with wrist force and then lifted immediately (see Fig. 4). Each point will be tapped repeatedly for 30 s and totally 6 min for each session. Acupuncturists should tap the points gently to make patients feel only a little pain and stop when the skin gets flushed but is not bleeding. The treatment will be two sessions per week for 12 weeks (24 sessions in all). Treatments will be done by acupuncturists with over 2 years of working experience and academic credentials above an undergraduate degree; they will be trained specifically for this protocol prior to the trial.

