### HRT group

HRT will consist of the following: (1) self-monitoring, (2) competing responses, (3) relaxation training, and (4) contingency management. Self-monitoring will be done to increase patients’ awareness of premonitory sensations or urges and to obtain detailed descriptions of varied tic symptoms. Patients will be provided with charts in which they can record the occurrence of tics, preceding sensations/urges, and the muscles and movements involved in a tic. Competing response training will involve each patient being trained to perform more appropriate physical responses when they feel the urge to perform tics, thereby preventing tic occurrence. For example, patients with arm jerking tics will be trained to contract the tic-opposing muscles when they are aware of the early sensations or urges preceding tics. For vocal tics, competing responses such as closing the mouth and breathing slowly through the nose will be used to avoid occurrence of tics. For complex tics, competing responses for individual components will be developed first and then chained. Patients will also be taught the relaxation techniques of thoracic breathing and diaphragmatic breathing. Treatment will typically be started with the patients’ most bothersome tics, unless the patient and clinician determine that competing responses for a less bothersome tic would be easier to implement before moving on to a more bothersome/severe/complex tic [17, 18]. The HRT training will be given weekly for 12 weeks (12 sessions in total) by a special rehabilitation therapist. The first two sessions will be 1.5 h, and the remaining sessions will be 1 h for each treatment.

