### Outcome measures

The primary outcome measure will be the mean change from baseline in the total tic score on the Yale Global Tic Severity Scale (YGTSS) at the 12th week.

Secondary outcome measures will include the mean change from baseline in the YGTSS score at the 4th, 8th, and 24th week, the mean score on the TS Clinical Global Impression Scale (CGI) at the 4th, 8th, 12th, and 24th week, and the mean score change compared with baseline on the Children and Adolescents’ Quality of Life Scale (CAQOL) at the 12th and 24th week.

Adverse events including fainting, stabbing pain during acupuncture, fatigue, insomnia, appetite change, worsening of symptoms, local infections, and other side effects related to acupuncture will be recorded in detail by patients, their parent/guardian, acupuncturists, and interviewers.

The outcome assessments will be done by research assistants who are blinded to the clinical management.

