## Discussion

Traditional plum-blossom needles pierce the skin when treating disease. However, to improve patient compliance in this proposed trial, we will use self-made blunt-pointed plum-blossom needles that will not pierce the skin and hence will alleviate the pain during treatment.

The primary aim of this study is to evaluate the effectiveness of plum-blossom needle therapy for TS. As the blunt-pointed plum-blossom needles will not pierce the skin, we cannot feasibly conduct sham plum-blossom needle therapy or placebo as a control group. HRT, recommended as an effective and safe TS treatment by the ESSTS, is the most extensively researched behavioral treatment for tics. Hence, comparing plum-blossom needle therapy with HRT will reflect the effectiveness and clinical value of plum-blossom needle therapy for TS. Most studies of HRT for TS have 10–14-week-long treatment, with follow-up data at 1 month to 1 year, mostly 3 months post-treatment. Thus, it is appropriate to conduct the follow-up visit at the 24th week after the last-time treatment [12, 19–21]. We will therefore measure the primary outcome at the 12th week, but we will also observe the changes in outcome measurements at the 4th, 8th, and 24th week to observe the time of onset and maintenance of the effect produced by plum-blossom needle therapy. In this trial, patients and acupuncturists will not be blinded, which means bias cannot be avoided. However, we can partially avoid biases caused by expectations and subjective assessment via rigid randomization, concealment of the allocation, and blinding of outcome assessors and statisticians. Otherwise, the outcome of this trial could not exclude the possible placebo effect of plum-blossom needle therapy, so we would not know its true efficacy.

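### Carrying the last entry forward for every missing value assumes the maintenance that week 24 is meant to test, and can dilute the week-12 comparison

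*Protocol article*

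**What the plan says.** The section on sample size and statistical analysis sets the analysis population: "The outcome parameters of randomized patients will be analyzed on an intention-to-treat basis". The next sentence is the missing-data rule: "Missing data will be replaced by the last entry". It is not limited to an endpoint, a visit or a reason for missingness. Continuous outcomes are then compared by a t-test or a nonparametric test. The same section allows for 20% dropout in the sample size, without a split by arm.

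The section on outcomes defines the main endpoint, which is taken at week 12: "The primary outcome measure will be the mean change from baseline in the total tic score on the Yale Global Tic Severity Scale (YGTSS"). The secondary outcomes include "the mean change from baseline in the YGTSS score at the 4th, 8th, and 24th week" and the "Clinical Global Impression Scale (CGI) at the 4th, 8th, 12th, and 24th week". CAQOL change is listed at weeks 12 and 24 only. The Discussion says that the measurements at weeks 4, 8 and 24 serve "to observe the time of onset and maintenance of the effect produced by plum-blossom needle therapy".

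**The concern.** Carrying the last entry forward treats a guess as an observation, and the guess is that the patient did not change after the last visit. Two uses of it matter here.

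- **Week 24.** A patient lost during follow-up is given the end-of-treatment score. No change since week 12 is what maintenance means, so the rule supplies part of the answer to the question that the visit asks. This needs no imbalance between arms.
- **Week 12.** A patient lost earlier enters with a week-8, week-4 or baseline score. If improvement accumulates over the 12 weeks, that score holds only part of the reduction the patient would have shown. The arm mean is pulled towards zero in proportion to dropout. Equal dropout dilutes a real difference. Unequal dropout creates or hides one.

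For CAQOL the only listed entry before week 12 is baseline, so an early leaver is scored as having no change. For CGI no baseline value is mentioned, so a patient lost before week 4 may have nothing to carry.

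**Working it through.** **Inputs from the protocol article.** Pilot 12-week reductions: 13.12 (SD 5.40) with the needle and 9.50 (SD 3.20) with HRT. One-sided α 0.025 for the design, two-sided 0.05 for the analysis. Power 80%, dropout 20%, 30 per arm.

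**The plan's own figure.** The difference is 13.12 − 9.50 = 3.62. The common SD is √((5.40² + 3.20²)/2) = 4.44. Then n = 2 × (1.960 + 0.842)² × 4.44² / 3.62² = 23.6, so 24 per arm, and 24/0.8 = 30. The stated 30 reproduces. It rests on 24 completers per arm, with dropouts treated as removed and not as kept with a carried score.

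**Assumptions, not in the documents.** A leaver's last entry holds a fraction f of that patient's 12-week reduction. If response is linear, f = 0, 1/3 or 2/3 for a last entry at baseline, week 4 or week 8; f = 1/2 lies between. Error rates and power come from 40,000 simulated trials of 30 per arm, with a two-sided 0.05 t-test.

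**Week 12, 20% dropout in both arms.** The expected difference is 3.62 × (1 − 0.20 × (1 − f)).

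| f | Expected difference | Power |
|---|---|---|
| 0 | 3.62 × 0.800 = 2.90 | about 44% |
| 1/3 | 3.62 × 0.867 = 3.14 | about 65% |
| 1/2 | 3.62 × 0.900 = 3.26 | about 76% |
| 2/3 | 3.62 × 0.933 = 3.38 | about 83% |

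For comparison, 24 completers per arm give about 79%. With no true difference, the type I error stays at about 5% for every f.

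**Week 12, assumed unequal dropout, no true difference.** Both arms improve by m = (13.12 + 9.50)/2 = 11.31, SD 4.44. The false difference is m × (1 − f) × (gap in dropout).

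| Dropout | f | False difference | Type I error |
|---|---|---|---|
| 15% v 25% | 2/3 to 0 | 0.38 to 1.13 | about 6% to 11% |
| 10% v 30% | 2/3 to 0 | 0.75 to 2.26 | about 10% to 31% |

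The sign follows the arm that loses more. With the pilot difference of 3.62 as the truth, 10% needle and 30% HRT dropout gives 4.13 (f = 2/3) to 5.16 (f = 0). With 30% needle and 10% HRT it gives 2.62 to 0.63.

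**Week 24, needle arm.** Let r be the share of the 12-week reduction still present and q the share lost after week 12. The reported reduction is 13.12 × ((1 − q) × r + q). Take q = 0.20, which borrows the 20% allowance and places it all after week 12.

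- r = 0: 13.12 × 0.20 = 2.62, where the truth is 0.
- r = 0.5: 13.12 × (0.40 + 0.20) = 7.87, where the truth is 6.56.

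**The case against.** The strongest reply is that the type I error figures rest on dropout splits that the documents do not contain. The article gives one figure, 20%, with no split. With equal dropout the error is nominal and the bias works against the needle claim. This stands, and it limits the point.

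A reader might infer unequal dropout from the visit schedules: "The treatment will be two sessions per week for 12 weeks (24 sessions in all") on one side, "The HRT training will be given weekly for 12 weeks (12 sessions in total") on the other. The documents do not support that step. The needle sessions last 6 minutes, so 24 × 6 min = 2.4 h in all. HRT takes 2 × 1.5 + 10 × 1 = 13 h. More visits and longer visits could offset each other, nothing says which arm would lose more patients, and stopping treatment is not the same as missing an assessment.

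A reader might also infer that every early leaver is penalised. That needs steady improvement in each patient, and the article gives only 12-week means. A patient who would have worsened after week 8 is flattered. Likewise, the week-24 bias towards maintenance holds if the effect wanes; if patients go on improving, the rule understates.

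Finally, sensitivity analyses may stand in a fuller protocol or analysis plan that is not shown, so their absence is no finding. The carry-forward rule itself is stated, and that is what is criticised.

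**Conclusion.** The point holds as a conditional criticism of a stated rule and should be fixed. The week-24 part is the firmest, because it follows from the rule and the stated purpose of the visit. Its size is the share lost after week 12 times whatever effect has gone by then, up to about 2.6 points with 20% lost. It concerns a secondary outcome.

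At week 12 the harm under the only dropout figure given is attenuation, not a false positive. Power can fall well below the planned 80% if leavers go early, but it is not harmed at f = 2/3. These results depend on the assumed response shape. Type I error inflation depends on unequal dropout, which is possible but not documented, and its direction is unknown. It would therefore be wrong to conclude that the primary test is invalid or that the rule favours the needle.

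**What to change.** Replace the missing-data sentence as follows.

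- **YGTSS.** A repeated-measures mixed model on observed scores at weeks 4, 8, 12 and 24, with baseline score, arm, visit and arm by visit. Use unstructured covariance, Kenward-Roger degrees of freedom and a stated simpler covariance as fallback, since only about 24 completers per arm are expected. Use a constrained baseline, or baseline as a response, so that all randomised patients are included; with baseline only as a covariate, patients without a later score would add nothing to the arm contrast. The week-12 contrast on the total tic score is primary. The week-24 contrast uses observed follow-up data.
- **CGI.** The same model on its observed visits.
- **CAQOL.** Multiple imputation with baseline CAQOL and the YGTSS visits as predictors. A repeated-measures model of CAQOL alone recovers nothing for patients lost before week 12.
- **Sensitivity.** Keep carrying forward only as a labelled sensitivity analysis, and add a delta-adjusted analysis over a prespecified range.

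The cost is slightly more programming and reliance on a missing-at-random assumption, which the delta analysis probes. No visits or patients are added. The article reports two participants recruited, so the change could be made before outcome data could influence it.

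### The primary change score is compared without baseline adjustment, which gives up precision, and the permitted rank test does not test the stated difference in means

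*Protocol article*

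**What the plan says.** Under Outcome measures, the protocol article defines the primary outcome as "the mean change from baseline in the total tic score on the Yale Global Tic Severity Scale" at week 12. Under Sample size and statistical analysis, it offers one method for every continuous outcome, the primary included: a t-test "or nonparametric test will be used for continuous data". It adds that "All outcome measures will be analyzed by two-sided tests" and "All significance levels will be established at 0.05".

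No baseline covariate is named, and neither of the two tests is singled out for the primary outcome. The sample size rests on the pilot reductions, 13.12 (SD 5.40) with plum-blossom needle therapy and 9.50 (SD 3.20) with habit reversal training. These are SDs of unadjusted change, so design and analysis both use baseline by subtraction only.

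**The concern.** Two things are at stake.

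**Precision.** Subtracting baseline fixes its coefficient at 1. Unless the week-12 score happens to rise point for point with baseline, a model that estimates the coefficient leaves less residual variance. The planned size has little reserve: 24 evaluable patients per arm for a nominal 80%. The score needed for the adjustment is already collected.

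**The question answered.** The primary outcome is a difference in mean change. A Mann-Whitney type test asks whether one distribution tends to give larger values than the other. The two questions can part when spreads differ and the data are skewed. The pilot SDs do differ, with a variance ratio of 5.40² / 3.20² = 29.16 / 10.24 = 2.85. Skewed data are also the usual reason for turning to a rank test.

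**Working it through.** **Inputs from the protocol article (Sample size and statistical analysis).** Pilot reductions 13.12 (SD 5.40) and 9.50 (SD 3.20); one-sided α 0.025; power 80%; dropout 20%; 1:1 allocation; 30 per group.

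**Inputs not in the document, so assumed.** The correlation ρ between baseline and week-12 scores, the SDs at those two visits, and the shape of the outcome distribution.

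**1. The plan's own figure**
- Difference: 13.12 − 9.50 = 3.62.
- Common SD: √[(5.40² + 3.20²)/2] = √19.70 = 4.438. Standardised effect: 3.62 / 4.438 = 0.816.
- n per arm = 2 × (1.960 + 0.842)² × 4.438² / 3.62² = 23.6, so 24.
- With dropout: 24 / 0.80 = 30. The stated number reproduces.
- One-sided 0.025 and two-sided 0.05 use the same critical value, so the analysis text is consistent with the sample size on this point.
- Power at 24 per arm is 80.7% by the normal approximation and 79.0% by the noncentral t. The noncentral t is used below.

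**2. Adjusting for baseline**

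Let k be the week-12 SD divided by the baseline SD. Then

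variance (adjusted) / variance (change score) = k²(1 − ρ²) / (1 + k² − 2ρk).

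With k = 1 this becomes (1 + ρ)/2. The residual SD is then 4.438 × √[(1 + ρ)/2], with 2 × 24 − 3 = 45 degrees of freedom.

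| Assumed ρ (k = 1) | Variance ratio | Residual SD | Power at 24 per arm |
|---|---|---|---|
| change score, unadjusted | 1 | 4.438 | 79.0% |
| 0.4 | 0.70 | 3.713 | 91.1% |
| 0.5 | 0.75 | 3.844 | 89.1% |
| 0.7 | 0.85 | 4.092 | 85.0% |
| 0.9 | 0.95 | 4.326 | 81.0% |

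The size of the gain depends on k:
- k = 1.25, ρ = 0.7: 1.5625 × 0.51 / (2.5625 − 1.75) = 0.797 / 0.8125 = 0.98, a gain of 2%.
- k = 1.25, ρ = 0.8: 1.5625 × 0.36 / (2.5625 − 2.00) = 0.5625 / 0.5625 = 1, no gain.
- k = 0.8, ρ = 0.5: 0.64 × 0.75 / (1.64 − 0.80) = 0.48 / 0.84 = 0.57, a gain of 43%.

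The first two cases follow from the best-fitting slope, which is ρk. At ρ = 0.8 and k = 1.25 it equals exactly 1, so subtraction is already optimal.

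**3. The rank test as a test of means**

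Simulated null trials with equal true means, SDs 5.40 and 3.20, 24 to 30 per arm, two-sided 0.05, 20,000 runs per setting:

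| Assumed shape | t-test rejects | Mann-Whitney rejects |
|---|---|---|
| normal | 5.1–5.2% | 5.1–5.3% |
| gamma, shape 2 | 5.2–5.6% | 10.0–11.0% |

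Unequal spread alone does little harm with equal arms. Unequal spread together with skewness roughly doubles the rate at which the rank test rejects equal means. The t-test stays close to nominal in both cases.

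**The case against.** The strongest reply is that nothing here is an error. Endpoint, sample size and t-test are consistent with one another, the t-test of change is unbiased under randomisation, and 30 per group is correct. That stands. The adjustment is a better use of the data, not a repair of an invalid analysis, and its benefit depends on quantities that the document does not give.

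Several stronger readings are tempting, and the document does not support them.

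- A reader might infer that baseline is discarded. It is used, but with a fixed coefficient.
- A reader might infer that subtraction over-corrects whenever ρ is below 1. That needs equal SDs at the two visits; the case k = 1.25, ρ = 0.8 is a counterexample.
- A reader might count chance baseline imbalance as a separate harm. It is the same loss seen from another side. At ρ = 0.5 and k = 1, a one-SD imbalance shifts the change-score difference by 0.64 points. The variance of that difference is (4.438 × √(2/24))² = 1.281² = 1.64, and 0.64² = 0.41 is 25% of it. That is exactly the 25% in the power table, and it is already inside the standard error.
- A reader might infer that the test will be picked after the data are seen. The article does not say when the choice is made. It is a condensed account, and a fuller plan may hold a rule. It also provides for a statistician independent of the research team and for blinding of statisticians. With equal spreads in the two arms, reporting the smaller of the two p-values would raise the error from 5% to about 5.6–6.5%; choosing by a normality pretest would leave it near 5%.

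Those safeguards limit partisan selection. They do not change what a rank test tests, and the article does name that test as an option for the primary outcome.

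**Conclusion.** The point holds as a recommended improvement to a stated method. It does not show bias, a wrong sample size or an invalid t-test.

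- **Precision:** with equal SDs at baseline and week 12, power at 24 evaluable per arm goes from 79% to between 91% (ρ = 0.4) and 81% (ρ = 0.9). The gain may be close to nil if the week-12 SD is larger than the baseline SD, and larger than tabulated if it is smaller. Since ρ and both SDs are unknown, the case for adjustment is firm but its size is not.
- **Rank test:** it is not a test of the stated mean difference. With the pilot SDs this is harmless for normal data and matters for skewed data, where about 10 to 11% of null trials reject equal means. That figure rests on the assumed gamma distribution with shape 2.

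**What to change.** State that the primary analysis is a linear model of the week-12 YGTSS total tic score (or its change) on treatment arm, with baseline total tic score as covariate and heteroscedasticity-robust standard errors, reporting the adjusted mean difference with its 95% confidence interval. Use the same form for YGTSS at the other visits and for CAQOL. Keep any rank-based test as a sensitivity analysis.

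The cost is one sentence of analysis wording and one degree of freedom. No new measurement is needed and the sample size can stay as it is. The Trial status section reports two participants recruited at the time of writing. The wording should be settled before outcome data are examined; if a fuller plan already contains it, confirming that is enough.

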**Discussion:**

This trial will evaluate the effectiveness and safety of plum-blossom needle therapy for TS compared with HRT. A limitation of this trial is that patients and acupuncturists cannot be blinded.

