At present, many parents in China seek treatment from Traditional Chinese Medicine practitioners for their children with TS. However, maintaining a fixed position during conventional acupuncture is difficult for children, and the pain associated with conventional acupuncture leads to poor compliance. Plum-blossom needle therapy is a method of shallow insertion of multiple needles into the skin. The treatment instrument is made of five or seven stainless-steel needles arranged in a plum-blossom-shaped pattern, hence the name ‘plum-blossom needle.’ Plum-blossom needle therapy treats diseases by tapping specific skin areas or acupoints corresponding to the treatment of different illnesses based on the meridian theory. Our pilot study in which we used self-made blunt-pointed plum-blossom needles showed that plum-blossom needle therapy can relieve the symptoms of TS. The treatment was well accepted by children with TS because of its mild pain as the needles did not pierce the skin.

This protocol is designed for phase II of our trial. The objective of this trial is to evaluate the effectiveness and safety of plum-blossom needle therapy for treating TS.

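### Apart from percentages, the only stated safety analysis is a significance test with 30 per arm, which cannot support a conclusion of safety or of equal safety to HRT

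*Protocol article*

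**What the plan says.** The Background section of the Protocol article names safety beside effectiveness: "The objective of this trial is to evaluate the effectiveness and safety of plum-blossom needle therapy for treating TS". The Discussion paragraph of the Abstract makes the comparison explicit: "This trial will evaluate the effectiveness and safety of plum-blossom needle therapy for TS compared with HRT". The main Discussion ranks the two: "The primary aim of this study is to evaluate the effectiveness of plum-blossom needle therapy for TS".

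Under Sample size and statistical analysis, safety has a sentence of its own: "For analysis of safety, the chi-square test or Fisher’s exact test will be done to compare the incidence of side effects between the two groups". Three general statements in that section also apply: "All outcome measures will be analyzed by two-sided tests"; "All significance levels will be established at 0.05"; and, on description, "categorical data will be represented by percentages".

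The number of patients, 30 per group with 20% dropout allowed for, comes from the pilot difference in YGTSS reduction alone. The article gives no expected side-effect rates and no rule for reading a non-significant safety comparison.

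**The concern.** A test of no difference can show that side-effect rates differ, in either direction. It cannot show that they are similar, or that the rate under the needle is low. A non-significant result is informative only if a relevant excess would probably have been detected, and at 30 per arm that is doubtful for moderate excesses.

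Some listed events, such as stabbing pain during acupuncture, can hardly occur under HRT. For those, the useful quantity is the rate in the needle arm and how high it could plausibly be. A between-arm p-value does not give that.

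At stake is the safety statement for a self-made device used in patients aged 7 to 18. If p > 0.05 were the only inferential result, there would be nothing else in the stated analysis, apart from bare percentages, on which to base that statement.

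**Working it through.** **1. The plan's own sample size.** Inputs from Sample size and statistical analysis: reductions of 13.12 (SD 5.40) and 9.50 (SD 3.20), one-sided α = 0.025, power 80%, dropout 20%.

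- Difference: 13.12 − 9.50 = 3.62.
- Mean variance: (5.40² + 3.20²)/2 = (29.16 + 10.24)/2 = 19.70, so SD = 4.44.
- n per arm = 2 × (1.960 + 0.842)² × 19.70 / 3.62² ≈ 23.6, rounded up to 24.
- With dropout: 24/0.80 = 30.

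The stated 30 reproduces. Nothing about side effects enters it.

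**2. How many events the safety test needs.** Take 30 per arm and no events under HRT.

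- Fisher, 5/30 vs 0/30: p = 2 × C(30,5)/C(60,5) = 2 × 142,506/5,461,512 = 0.052, not significant.
- Fisher, 6/30 vs 0/30: p = 2 × C(30,6)/C(60,6) = 2 × 593,775/50,063,860 = 0.024, significant. Six events are needed.
- Uncorrected chi-square, 3/30 vs 0/30: 0.10²/(0.05 × 0.95 × 2/30) = 3.16, below 3.84. For 4/30 vs 0/30: 0.1333²/(0.0667 × 0.9333 × 2/30) = 4.29, above 3.84. Four events are needed.

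If the true rates are 10% and 0%, power is the binomial probability (n = 30, rate 0.10) of reaching that count. This is 7.3% for six or more (Fisher) and 35.3% for four or more (chi-square). The miss probabilities are 92.7% and 64.7%.

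**3. Power over a range of assumed rates.** For each pair of rates, all 31 × 31 possible tables were listed and the binomial probabilities of those with p ≤ 0.05 were summed. The switch rule uses Fisher when any expected count is below 5 and uncorrected chi-square otherwise.

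| Needle vs HRT (assumed) | Fisher | Switch rule | Uncorrected chi-square |
|---|---|---|---|
| 10% vs 0% | 7.3% | 7.3% | 35.3% |
| 15% vs 0% | 28.9% | 28.9% | 67.8% |
| 20% vs 0% | 57.2% | 57.2% | 87.7% |
| 20% vs 5% | 24.1% | 27.5% | 45.3% |
| 30% vs 10% | 37.2% | 46.8% | 49.9% |
| 40% vs 5% | 89.3% | 92.9% | 94.3% |

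At 10% vs 0% the expected counts are well below 5, so Fisher is the likely choice there. With 24 completers per arm, power is 8.5% (Fisher) or 21.4% (chi-square) for 10% vs 0%, and 23.7% or 36.5% for 20% vs 5%.

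**4. What intervals would show from the same data.**

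- 5/30 vs 0/30: Fisher p = 0.052; Newcombe 95% interval for the difference 2 to 34 percentage points.
- 3/30 vs 0/30: p = 0.24; interval −3 to 26 points.
- 0/30 in one arm: exact two-sided 95% upper limit 1 − 0.025^(1/30) = 11.6%.

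**The case against.** The strongest reply is that the article draws no such conclusion. It says safety will be evaluated, not that p > 0.05 will be called safe. The test is conventional and valid, effectiveness is the primary aim, and a trial of this size is normally powered on its primary outcome alone. Percentages per arm are already planned, and a condensed article may leave intervals and wording to a fuller document.

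Much of this stands. A reader might infer that the sponsor intends to claim safety from non-significance; no sentence says so. A reader might also infer that the test can only go against the needle. It is two-sided, and fatigue, insomnia or worsening of symptoms can occur under HRT, so it could favour either arm. Nor is p > 0.05 likely whatever the harm: the result depends on assumed rates and on which of the two named tests is used, and large excesses would usually be found. Low power for safety is not in itself an error of design.

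What does not stand is that the method was simply left for later. The article names an inferential method for a stated objective, and that method cannot deliver a conclusion of safety or comparability. Percentages alone do not repair this, because they carry no measure of uncertainty.

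**Conclusion.** The point holds as a mismatch between a stated objective and the method named for it. If the true rates were 10% vs 0%, the planned test would miss the excess with probability 93% (Fisher) or 65% (uncorrected chi-square); at 20% vs 5%, with probability 76% or 55%. For 20% vs 0% the miss probability ranges from 43% to 12%, and for 40% vs 5% from 11% to 6%. These figures assume 30 analysed per arm and two-sided 0.05. All the rates are assumptions.

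This is a worthwhile, inexpensive improvement. It does not affect the primary analysis, and it is not an argument for a larger trial.

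**What to change.** In Sample size and statistical analysis, base the safety conclusion on estimation:

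- Report the number and percentage of patients per arm with any side effect, and with each listed event, with exact (Clopper-Pearson) 95% intervals.
- Report the between-arm risk difference with a 95% interval, for example Newcombe's.
- Keep the chi-square or Fisher p-value as descriptive only. It can disagree with the interval near the boundary, as 5/30 vs 0/30 shows.
- State that p > 0.05 will not be read as evidence of safety or of equal safety to HRT, and that 0/30 events still leaves an upper limit of about 12%.

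This takes a few sentences and a few table columns, with no new data or patients. Trial status reports two participants recruited at the time of writing. The price is a more cautious safety statement.
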